**Figure 1 F1:**
[figure not shown]
Summary of the study design and theoretical framework.

## Methods and analysis

### Study population

This study will include a cross-sectional questionnaire followed by a 2-week digital phenotyping component in a subsample. For the cross-sectional questionnaire, we will recruit 1000 adolescent and adult gamers from the general population in the province of Quebec, Canada. Eligibility criteria will include: (1) Age 16–25 years, (2) Playing video games at least 1 hour per week and (3) Speaking English or French. Of this sample, 100 participants will be selected to participate in the digital phenotyping component; these participants will be randomly selected after stratification according to their gender (to ensure at least 30% of cisgender boys or men, at least 30% of cisgender girls or women and at least 10% of transgender or non-binary individuals). Digital phenotyping will include daily surveys (sometimes referred to as ecological momentary assessment or experience sampling^55^) and mobile sensing. The daily surveys and mobile sensing data will be collected for 2 weeks using the Beiwe application installed on participants’ smartphones.

### Rationale for the sample size

Given the variety of objectives and analyses planned, we established the sample size based on two basic scenarios: a linear regression of one cross-sectional variable over another (n=1000) and a generalised linear mixed model where one daily digital phenotyping variable is regressed over another (n=100). For the cross-sectional scenario, we conducted the power analyses in G*Power, V.3.1.9.7. We calculated that a sample of n=1000 will be sufficient to detect a linear regression slope of β=0.09, assuming a type I error rate of 0.05 (two-tailed) and statistical power of 85%. This would be sufficient to evaluate, for example, a weak but significant association between greater belonging and lower levels of psychotic-like experiences (Objective 1) or a greater propensity for immersion and greater psychological functions of games (Objective 2). For the digital phenotyping component, we used the sample size calculator developed by Barnett and colleagues:^56^
https://onnela-lab.shinyapps.io/digital_phenotyping_sample_size_calculator/. We found that a sample size of 100 persons with daily measures over 2 weeks will provide statistical power of 93% to detect effect sizes of β=0.07 with a type I error rate of 0.05, assuming 50% missing data and random-effect variance of 1.1. These parameters would be sufficient to examine the association between daily needs satisfaction in games and daily well-being (Objective 1) or the association between daily immersion and daily well-being (Objective 2). This statistical power estimation also applies to passive sensor data (eg, geolocation) transformed into daily features (eg, daily time spent at home).

### Procedures for recruitment, data collection and retention

Recruitment for the cross-sectional study started on 15 September 2024 and is ongoing. Participants are recruited through advertisements on social media targeting the age range and geographic region of interest. To maximise sample diversity, we have contacted several community organisations with missions related to mental health, LGBTQ+communities, and the well-being of immigrant and racialised youths, as well as university student groups and online communities with game-adjacent interests (eg, roleplay games, cosplay, geek) across the province of Quebec who circulated the advertisement through their networks. Recruitment will stop after achieving the targeted sample size. After being directed to a website presenting the study, individuals will be screened for eligibility and will provide virtual consent to participate in the cross-sectional questionnaire via electronic signature. Participants will then complete the cross-sectional questionnaire on REDCap, after which they will be invited to complete additional measures (cognitive tasks) on PsychoJS, which will be described in a future publication. Participants who provide optional consent to complete the cognitive tasks on PsychoJS will receive a link by email at a later time.

As part of the cross-sectional questionnaire, participants will be asked if they agree to be contacted for the digital phenotyping component. Participants of the digital phenotyping component will be randomly selected by email or phone from the list of responders who expressed their interest and will be invited to a 30 min virtual individual meeting with a research assistant. During the meeting, the research assistant will present the study protocol and consent form for the digital phenotyping. Consent will be provided by electronic signature. Then, participants will receive assistance to install the Beiwe application on their smartphone.

To compensate participants for their time, they will be offered $35 in gift cards for participating in the cross-sectional survey. Participants in the digital phenotyping will receive $5 for each daily questionnaire completed (ie, a total of $70 if all questionnaires are completed). Throughout the follow-up period for digital phenotyping, a research assistant will be available to provide technical support as needed. An email will be sent to participants when they reach the fourth day of data collection to inquire about any difficulties.

### Beiwe application

Throughout the follow-up period, Beiwe will be used to collect passive digital data and to administer self-report questionnaires to participants of the digital phenotyping. This application is compatible with iOS and Android smartphones and automatically uploads the data it collects to secure cloud servers. Beiwe was developed by the Onnela Lab (Harvard University) and implemented in Montreal by [name] and colleagues (Centre Axel). It can be downloaded from the Centre Axel website (https://beiwe.centreaxel2.com/download) for Android phones and from the App Store for iOS phones. Participants will be instructed to let the application run in the background throughout the 2-week follow-up period. The app will passively collect data on geolocation, accelerometry and screen activation time. Data from Beiwe will be encrypted and stored on secure servers in Quebec. Every day for 2 weeks, participants will also receive a prompt to complete a questionnaire on the application. Previous studies^39 57^ support the association of these digital markers with common mental health symptoms in population-based samples, when combined with self-report questionnaires, and will be explored here as correlates of game-related experiences and well-being.

### Cross-sectional measures

*Eligibility screening*. Questionnaires are available in the online supplemental material. Participants will report their age, year of birth, place of residence (province of Quebec: yes or no), and time spent on video games in a typical week (eight options, ranging from none to more than 20 hours per week).

*Demographic questions*. Participants will report their sex assigned at birth (male, female or intersex), gender (woman, man, non-binary, two-spirit or other), and ethnoracial identity (Arab or Middle Eastern, Asian, Black or African, Hispanic or Latinx, Indigenous, Mixed, Other or White). Participants will also report their highest level of education completed (11 options), student status (full-time, part-time or none) and employment status (full-time, part-time or none). Participants will optionally provide their postal codes for future secondary analyses of neighbourhood-related features. Lastly, participants will be asked whether they self-identify as someone with a disability (yes or no), if they have ever been diagnosed with a mental health condition, what the diagnosis was (open textbox), and if they have ever sought help or services for mental health.

*Game-related experiences and practices*. Participants will report whether they self-identify as a gamer (yes or no) and at what age they started playing games regularly. The frequency of play of 13 game genres will be reported on a scale of 1=never to 5=very often using a questionnaire adapted from Allen.^58^ Psychological functions of gaming will be assessed using a modified version of the Fandom Functions Scale,^59^ which includes 14 items evaluating the role of fan practices in providing a sense of purpose (eg, ‘Provides me with an opportunity to grow and discover more about aspects of myself’), an escape from stressors (eg, ‘Provides me with a break from life’s stresses’) and belonging (eg, ‘Provides me with a chance to expand my circle of friends’). The three subscales displayed good internal reliability (respectively α=0.93, α=0.86 and α=0.84) and were correlated with well-being and fandom identity in a previous sample of undergraduate students in the US.^59^ The opening instruction of the scale, which broadly inquired about the person’s fan interests, was modified to target participants’ ‘involvement with video games and the game community’. The use of games to recuperate from stress will be evaluated using four items adapted from the Recovery Experience Questionnaire (eg, ‘When I play video or computer games I forget about work’) rated on a scale of 1=does not apply at all to 5=does fully apply.^60 61^ The full questionnaire, tested in a sample of young adults in Germany, included four subscales (total 16 items), psychological detachment: α=0.78, relaxation: α=0.70, mastery: α=0.76, control: α=0.77, which were positively associated with greater time spent on gaming.^60^ Game play with friends, family or romantic partners, whether in person or remotely, will be reported using one item on a scale of 0=no participation to 4=at least daily, with a follow-up item inquiring about the general length of these play sessions.^61 62^ An additional, secondary measure of gaming motivations will be the Video Game Uses and Gratifications Instrument, which includes 20 items (eg, ‘I feel proud when I master an aspect of a game’) rated on a scale of 1=strongly disagree to 5=strongly agree.^63^ The questionnaire was validated in a sample of children, adolescents and university students in the US and includes six subscales (competition, challenge, social interaction, diversion, fantasy and arousal) with good internal reliability (range of α: 0.80–0.89) and positive associations with time spent playing video games. Problematic gaming will be assessed with the Gaming Disorder Test, which includes four items (eg, ‘I have difficulties controlling my gaming activity’) on a scale of 1=never to 5=very often.^64^ The scale displayed good internal reliability (α=0.84) in a sample of adult gamers in China and the UK and was positively associated with depression, loneliness and another validated measure of gaming disorder. Exposure to and perpetration of bullying in video games will be measured using three items adapted from the Olweus Bullying Questionnaire (eg, ‘How often have you been bullied while gaming in the past couple of months?’) rated on a scale of 1=never to 5=several times a week.^65^ Lastly, participants will be invited to write in open-ended textboxes about their reasons for gaming, what they like about playing video games, a time where playing games helped their mental health, a time where playing games worsened their mental health, their favourite games growing up and now, what game character they would like to be and why, and whether they feel games have an impact on their daily life and well-being.

*Streaming-related experiences and practices*. The questions in this section were modelled on those related to gaming but were adjusted to focus on watching or producing game streams. Since these modified questionnaires have not been validated, they were pilot-tested by the research team and Youth Advisory (see Patient and public involvement, below), and their psychometric properties will be examined in the present study (see Analyses, below). Participants will first be asked, ‘Do you consider yourself a streamer and/or someone who watches video game streams?’ (yes or no), and subsequent questions will only be administered if they answer ‘Yes’. Measures in this section will include streaming-focused versions of the above measures: weekly time spent on watching others play games and on streaming games, age at beginning of these activities, preferred genres (same as above), preferred platforms (eight items, eg, Twitch, YouTube, etc), a modified Fandom Functions Scale,^59^ the four items from the Recovery Experience Questionnaire,^60^ the frequency of watching or streaming with others,^62^ a modified Video Game Uses and Gratifications Instrument,^63^ a modified Gaming Disorder Test^64^ and bullying in streaming platforms.^65^ Open-ended questions will be administered regarding motivations for using streaming platforms, favourite streamers and perceived impacts on daily life and well-being.

*Personality*. Propensity for immersion will be measured with the Modified Tellegen Absorption Scale, which includes 34 items (eg, ‘The crackle and flames of a woodfire stimulate my imagination’) rated on a scale of 1=never to 5=always.^66^ This questionnaire showed good internal reliability, α=0.94 in a sample of college students in the US^67^ and has been associated with a range of traits and experiences, such as the propensity for immersion in media, hypnosis and dissociation.^68^ Personality traits of extraversion, agreeableness, conscientiousness, neuroticism and openness will be measured with the short version of the Big Five nventory, which includes 10 items (eg, ‘I see myself as someone who is reserved’) on a scale of 1=disagree strongly to 5=agree strongly, and has demonstrated good validity in adult samples in the US, Germany and France.^69 70^

*Other psychological variables*. Psychotic-like experiences will be measured with the Current Community Assessment of Psychic Experiences, which includes 15 items (eg, ‘In the past 3 months, have you felt as if the thoughts in your head are not your own?’) rated on a scale of 1=never to 4=nearly always.^71 72^ The scale displayed good internal reliability (α=0.84) and was positively associated with psychological distress in a sample aged 16–25 in Australia.^71^ Social support will be measured with the Oslo Social Support Scale, which includes three items assessing the number of people close to the person, how much interest others show in the person, and how easy it is to get help when needed.^73^ Usage in the past 2 weeks of energy drinks, alcohol, cannabis, amphetamines, non-prescribed psychostimulants and other substances will be reported on a scale of 1=never to 4=every day.^74^ Cognitive functioning will be assessed using interactive cognitive tasks on a separate platform in a subset of voluntary participants; these measures will be reported elsewhere as part of a secondary study.

### Daily surveys

*Well-being, sleep and mood*. Daily well-being will be measured with a questionnaire from the WARN-D study,^75^ which includes 10 items (eg, ‘Today, I felt down or depressed’) on a scale of 1=not at all to 7=very much. We added an additional item for somnolence (‘Today, I felt sleepy’) as a marker of sleep insufficiency. Sleep schedules will be assessed using three items from the Munich Chronotype Questionnaire (eg, ‘What time did you go to bed last night?).^76^ Affect will be assessed using a short version of the Positive and Negative Affect Schedule,^77^ with eight items (eg, ‘Today, I felt stressed’) on a scale of 1=not at all to 7=very much. In a sample of university students in the Netherlands, the scale demonstrated configural and metric invariance over different sampling frequencies and questionnaires length, and it was found to have good reliabilities for positive and negative affect at the within-person level (ω=0.818 and ω=0.815) and between-person level (ω=0.934 and ω=0.929), respectively.

*Social interactions and daily events*. Participants will report daily occurrence of in-person social interactions with two items adapted from the WARN-D questionnaire,^75^ assessing relationship categories (eg, friends, family, strangers) and the degree of enjoyment (1=not at all to 7=very much). Two more items will assess virtual social interactions following the same format. Daily events were reported using four items from the WARN-D questionnaire about the categories of most positive and negative events of the day (eg, finances, physical well-being, etc) and their intensity (1=not at all positive/negative to 7=very positive/negative).

*Gaming*. Participants will report daily instances of gaming (yes or no) and periods of the day where they played using two items adapted from Allen^58^ and Gentile *et al*.^78^ Positive social experiences (eg, receiving praise, good atmosphere) and experiences of bullying, harassment or exclusion in games will be reported on a scale of 1=never to 5=very often using 10 items from Hygen *et al* (soon to be submitted). The satisfaction and frustration of psychological needs in games will be reported using the Basic Needs in Games Scale, which includes 18 items (eg, ‘I could play the games in the way I wanted’) rated on a scale of 1=strongly disagree to 7=strongly agree.^79^ Immersion will be measured with the immersion subscale of the Player Experience Inventory, which includes three items (eg, ‘I was no longer aware of my surroundings while I was playing’) rated on a scale of 1=strongly disagree to 7=strongly agree.^80^ Prosocial behaviours in and out of games will be measured with three items adapted from Pronizius *et al*^81^ (eg, ‘Today, have you helped or supported a non-playable character in a video game?’; yes or no).

*Streaming*. Daily instances of streaming or watching game streams will be reported using two items similar to those for gaming. The satisfaction and frustration of psychological needs through streaming activities will be evaluated using a modified version of the Basic Needs in Games Scale.^79^ Immersion will be measured using a modified version of the immersion subscale of the Player Experience Inventory.^80^

### Patient and public involvement

This study is part of Game-in-Action, a larger project that aims to better understand the impacts of video games on the mental health of young people and to develop new intervention strategies. The project is based at the Ludic Mind Studio, a digital incubator led by the senior author, [name]: https://www.mcgill.ca/ludicmind/. Based on the principles of integrated knowledge translation^82^ and the Strategy for Patient-Oriented Research framework,^83^ Game-in-Action engages youth, parents, researchers, clinicians and institutional-level and provincial-level decision-makers in designing the project and supporting its implementation. These frameworks ensure that the project activities and outcomes will ultimately achieve meaningful benefits for Quebec youth, for the adults close to them (eg, parents, educators, social/health providers), and for social and health services in the province. We established a multi-sectoral and multi-stakeholder Advisory Committee (AC) at the outset to provide oversight at all stages of the project. The AC includes members from the provincial Quebec health ministry, social and health services, the video game industry and youth of the Gaming Against Stigma Advisory Group (Youth Advisory). The Youth Advisory includes gamers aged between 18 and 35 years old, some with lived experience of mental illness.

The Youth Advisory and the Ludic Mind Studio research team meet every month to discuss their research activities and knowledge translation projects. The Youth Advisory was involved from the beginning of the present study (study design and application for funding) in April 2023. The rest of the AC was formed after obtaining funding in September 2023. Since then, we have been holding joint meetings with the AC approximately every 6 months, in addition to monthly meetings with the Youth Advisory. The AC and Youth Advisory contributed to the present study’s research questions by advocating for the inclusion of streaming-related measures based on their personal experiences of streaming as an important part of game culture. The AC also supported the foregrounding of social factors as part of the theoretical framework and research questions of the study, notably to acknowledge the role of games for coping with challenging life circumstances. The selection of measures was made by the research team based on these considerations and was presented to the AC, who approved it. The Youth Advisory supported recruitment by disseminating the study invitation in their networks. Members of the Youth Advisory tested the cross-sectional survey to confirm that the time for completion of the survey was acceptable, and some changes were made based on their feedback (eg, relabeling a ‘Clinical factors’ category, which includes psychotic-like experiences, as ‘Psychological factors’ instead). The Youth Advisory will be similarly involved in testing the longitudinal and mobile sensing measures, which are in the process of being implemented. After completion of the study, we will present our preliminary results to the AC to obtain their feedback and include their perspective in the interpretation and dissemination of the results.

### Analyses

We will conduct quantitative analyses in R (R Foundation for Statistical Computing). Characteristics of the analytic samples (cross-sectional and longitudinal) will be described to identify the potential underrepresentation of groups (eg, gender, ethnoracial, socioeconomic or rural vs urban groups) that may limit the generalisability of findings. Using lavaan,^84^ we will examine the factor structure and internal consistency of ad-hoc or modified questionnaires, and, for analyses of longitudinal changes over time, we will also test for longitudinal measurement invariance.^85^ Statistical significance will be defined as p<0.05 or 95% CIs not overlapping the null. We will apply correction for false discovery rate using the Benjamini and Hochberg^86^ method when multiple predictors are tested for a single hypothesised outcome (eg, there are two predictors of psychotic-like experiences for Objective 1: play time with family, friends or romantic partners, and the modified Fandom Functions Scale—Belonging). We will analyse cross-sectional outcomes using generalised linear models adjusted for relevant socio-demographic characteristics (eg, sex, educational attainment and occupational status). In these models, missing data will be handled by complete case analysis or multiple imputation. We will analyse longitudinal outcomes (eg, daily well-being) using generalised linear mixed models with observations nested in individuals. Missing data will be handled by maximum likelihood. To parse out within-person and between-person associations between longitudinal repeated measures (eg, the association between daily psychological need satisfaction and daily well-being), we will apply person-centring and mean-centring to the predictors; this approach accounts for time-invariant, unmeasured individual factors that could confound associations between the predictor and outcome.^55^ Mobile sensing data will be transformed into higher-level, validated features over epochs of 1 day for integration into generalised linear mixed models as exploratory predictors of game-related experiences and well-being; for example, geolocation data will be used to infer the daily amount of time spent at home.

Of note, because the digital phenotyping component will only start after completion of the cross-sectional sample, we anticipate that for some participants, the interval between the two data collections may be up to about 12 months. We will consider the impact of this delay on the interpretation of the eventual study findings. For example, the delay could attenuate the strength of the association between modified Fandom Functions Scale—Belonging (cross-sectional) and daily well-being (digital phenotyping) in Objective 1, given that the experience of belonging in game communities may change with time.

We will use reflexive thematic analysis for qualitative data.^87^ This approach aims to uncover shared patterns of meaning across participants’ responses through a reflexive, recursive process. The steps of reflexive thematic analysis include: (1) Familiarisation with the data, (2) Generating initial codes, (3) Searching for themes, (4) Reviewing potential themes and (5) Defining and naming the themes.^88^ Our analysis of the qualitative data will be primarily inductive to better understand the lived experiences of gamers. Finally, in collaboration with the AC, the quantitative and qualitative results will be integrated within a critical realist framework to support or revise the theoretical interpretations.^89^

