*Objective 1. To examine whether the satisfaction of psychological needs and social affiliation through games is associated with well-being* Hypothesis: Greater play time with others, higher scores for belonging and need satisfaction, and lower scores for need frustration will be associated with lower levels of psychotic-like experiences and higher levels of well-being		
Play time with others (C) Fandom Functions Scale—Belonging (C) Basic Needs in Games Scale, gaming and streaming (L)	Psychotic-like experiences (C) Daily well-being questionnaire (L)	Lifespan developmental history; Cultural meaning, norms, values and affordances
*Objective 2. To examine whether a greater propensity for immersion is associated with better satisfaction of psychological needs and improved well-being through games* Hypothesis: Higher scores for absorption and daily immersion will be associated with higher levels of fandom functions, need satisfaction and daily well-being, but also higher levels of psychotic-like experiences and problematic gaming		
Tellegen Absorption Scale (C) Daily immersion (L)	Fandom Functions Scale (C) Basic Needs in Games cale, gaming and streaming (L) Daily well-being (L) Psychotic-like experiences (C) Problematic gaming (C)	Lifespan developmental history
*Objective 3. To examine the associations of marginalised identities with exposure to harassment and discrimination in games or streaming, and the mediated associations with well-being* Hypothesis: Participants identifying as female, transgender or non-binary, from an ethnoracial minority, or having a history of mental health problems will report higher levels of exposure to bullying, which will mediate an association with lower levels of daily well-being		
Sex and gender (C) (Dis)ability (C) Racialised identity (C) History of mental health problems (C)	*Mediator:* Exposure to bullying (C, L) Daily well-being (L)	Social structures and positioning
*Objective 4. To explore young people’s narratives about the role of games and streaming in their lives and their mental health* This exploratory objective has no hypothesis and will rely on qualitative data from open-ended questions (C)		
N/A	N/A	Individual biography and self-understanding

C, cross-sectional sample (n=1000); L, longitudinal, digital phenotyping subsample (n=100).

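### Objective 1 predicts daily well-being from survey-only Belonging and shared-play scores that may be up to about 12 months old, and the plan responds only by interpretation

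*Protocol article*

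**What the plan says.** In Table 1 the predictor cell for Objective 1 reads "Play time with others (C) Fandom Functions Scale—Belonging (C) Basic Needs in Games Scale, gaming and streaming (L" (closing bracket cut), where C marks the survey and L the digital phenotyping subsample. Daily well-being (L) is one of the two outcomes. Belonging and shared play therefore come from the survey alone, while need satisfaction comes from the diary.

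The Analyses section explains the timing: "the digital phenotyping component will only start after completion of the cross-sectional sample". It follows that "we anticipate that for some participants, the interval between the two data collections may be up to about 12 months". The authors name the consequence: "the delay could attenuate the strength of the association between modified Fandom Functions Scale—Belonging (cross-sectional) and daily well-being". Their response is one sentence: "We will consider the impact of this delay on the interpretation of the eventual study findings".

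Two other statements bear on what could be done. Under Procedures for recruitment, data collection and retention, each person selected for phenotyping "will be invited to a 30 min virtual individual meeting with a research assistant"; the listed content is the study protocol, consent and installation of the app. Under Patient and public involvement: "The Youth Advisory will be similarly involved in testing the longitudinal and mobile sensing measures, which are in the process of being implemented".

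**The concern.** How much someone plays with others, and how far they feel they belong in a game community, can change over a year; the authors say so for belonging. If the old score relates to present well-being only through the present level of the same trait, the observed association shrinks in proportion to the stability of the score over the delay. The shrinkage is uneven. Because phenotyping waits until the survey sample is complete, the earliest respondents have on average the oldest scores.

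At stake is how a weak or null result for these two predictors is to be read. It could mean that belonging and shared play matter little for daily well-being, or only that the scores were out of date. Discussion after the fact cannot separate the two.

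**Working it through.** **1. Is there a fresh value anywhere?** The Daily surveys section lists well-being, sleep, affect, social interactions, daily events, gaming, in-game social experiences, need satisfaction, immersion, prosocial behaviour and streaming. It does not list the Belonging items or the frequency and length of shared play. No repeat questionnaire is described for the onboarding meeting. No delay term or sensitivity analysis is described under Analyses.

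**2. The plan's own figures.** The 12-month interval is an expectation and cannot be derived: the protocol gives a recruitment start (15 September 2024) but no end date or accrual rate. The power formula can be checked against the survey scenario under Rationale for the sample size. With noncentrality sqrt(n) × r / sqrt(1 − r²) and n − 2 degrees of freedom:
- n=1000, slope 0.09, two-sided 0.05 gives 81.5% power.
- The slope detectable with 85% power is 0.094, which rounds to the stated 0.09. The statement agrees within rounding.

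The 93% for β=0.07 comes from an online calculator whose full inputs are not given, so it was not reproduced. It covers a daily variable regressed on another daily variable, not a survey score predicting diary outcomes.

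**3. What n=100 offers for a person-level predictor.** The same formula gives a detectable correlation with a person's mean daily well-being of about 0.27 (80% power) or 0.29 (85%), before any delay.

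**4. Effect of the delay.** The protocol gives neither an effect size nor a stability for this analysis, so both are assumed:
- true person-level correlation 0.30;
- 12-month stability s from 0.5 to 0.9, decaying exponentially with time;
- delays spread evenly over 0 to 12 months.

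Average stability is then (s − 1) / ln(s), and the observed correlation is 0.30 times that.

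| 12-month stability | Average stability | Observed correlation | Power, n=100 |
|---|---|---|---|
| fresh score | 1.00 | 0.300 | 88% |
| 0.9 | 0.949 | 0.285 | 84% |
| 0.8 | 0.896 | 0.269 | 79% |
| 0.7 | 0.841 | 0.252 | 73% |
| 0.6 | 0.783 | 0.235 | 67% |
| 0.5 | 0.721 | 0.216 | 59% |

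Worked line for s=0.5: (0.5 − 1) / ln(0.5) = 0.5 / 0.693 = 0.721; 0.30 × 0.721 = 0.216; noncentrality 10 × 0.216 / sqrt(1 − 0.216²) = 2.21; power 59%. For the fresh score the noncentrality is 10 × 0.30 / sqrt(1 − 0.09) = 3.14; power 88%.

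For an assumed correlation of 0.20, power is 52% with a fresh score and 30% to 48% over the same stability range. All these figures precede the planned false discovery rate correction and covariate adjustment.

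**The case against.** The authors do not hide the problem. They state the delay, its cause, its likely direction and an affected example, and nothing in the protocol contradicts itself here. That stands; the point is the response, not the disclosure.

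A concurrent score also changes the question. It brings predictor and outcome closer in time, so current mood is more likely to colour both. Preferring the earlier score is a defensible choice, which is why the survey-score analysis should be kept. That the onboarding meeting has room for questions is an inference, since its stated content is already protocol, consent and app installation. The diary also records positive social experiences in games and virtual interactions, but these are not the two measures that Table 1 names as predictors.

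A reader might infer more than the documents support:
- **That the bullying mediator in Objective 3 is equally out of date.** The survey item does look back over a limited window ("How often have you been bullied while gaming in the past couple of months"), but Table 1 marks the mediator as C and L, and the daily survey asks about bullying, harassment or exclusion in games.
- **That people who have stopped gaming would go unnoticed.** The diary records each day whether the person played, so they can be identified.
- **That power falls to 32% to 44%.** For a correlation of 0.30, those values need an average stability of 0.5 to 0.6 across all 100 participants. The protocol says the delay may reach about 12 months for some.
- **That the stated 93% power is undermined.** It refers to daily-on-daily associations, which the delay does not touch.

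**Conclusion.** The point holds for two survey-only predictors, Belonging and play time with others, against one outcome, daily well-being. The plan foresees a bias towards zero in a main objective and leaves a preventive step unused. On the assumed values, power falls from 88% to between 59% and 84%. The true loss could lie outside that range if the stability, the effect size or the spread of delays differs, and it would be smaller if past belonging had a lasting effect of its own.

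Not affected are the within-person daily analyses, the need-satisfaction and immersion analyses based on diary measures, and the psychotic-like experiences analyses with survey data on both sides. Absorption, a propensity measure, and the identity variables should be far less sensitive to the delay. This is a worthwhile improvement rather than a flaw that invalidates the study. It has to be made before phenotyping data are collected.

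**What to change.** - **Re-measure.** At onboarding to digital phenotyping, re-administer the Belonging items and the shared-play frequency and length items. A self-completed link is preferable, because it matches the mode of the survey and does not depend on time in the meeting.
- **Analyse.** Use these scores as the Objective 1 predictors of daily well-being.
- **Keep the survey scores as a sensitivity analysis** with a predictor-by-delay interaction. A main effect of days since the survey would not help: it shifts the level of well-being but does not correct the attenuated slope.
- **Optional.** Re-ask the three survey bullying items and weekly play time. In-game bullying and daily gaming are already in the diary.

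**Cost.** Shared play is one item plus a follow-up, and Belonging is one of three subscales in a 14-item scale. The burden is therefore a few minutes for 100 people, with a likely minor ethics amendment. The remaining price is less temporal separation between predictor and outcome, which the retained survey-score analysis offsets.
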